### Patient safety

In the process of acupuncture treatment, possible adverse events (AEs) including subcutaneous hematoma, infection, alcohol allergy, etc., will be observed in detail and documented in the CRFs. Causality between acupuncture and AEs will be assessed. If serious AEs do occur, the grouping will be un-blinded and we will report the AE to the project leader (PL) and Ethics Committee immediately, who will make a decision on whether the participant needs to be withdrawn from the study, or whether the trial should be adjusted or terminated. For those who suffer harm from trial participation, we will treat them free of charge until they recover.

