## Background

Worldwide, stroke is a leading cause of death and disability [1–3]. A patient with a history of stroke is more vulnerable to recurrence [4, 5]^.^ Especially in China, the recurrence rate of stroke is higher than that of western countries [6, 7]. Recurrent stroke demonstrates higher mortality and disability rates than the previous stroke, which is a heavy burden on both health care resources and society in general [7, 8]. Ischemic stroke is the most common type of stroke and 72.7% of Chinese ischemic stroke patients also suffer from hypertension [6], an independent risk factor for stroke recurrence [9]. Therefore, it would be of great benefit in combating stroke recurrence to decrease blood pressure (BP).

Antihypertensive medications have been regularly used to reduce BP; however, low adherence to antihypertensive medications is prevalent due to various factors including prior experience of medication side effects [10], leading to poor BP control [11]. Uncontrolled BP maybe related to side effects or interactions of antihypertensives and this observation is more commonly noted in older populations [12, 13]. Moreover, a former meta-analysis has shown that only angiotensin-converting enzyme inhibition (ACEI) plus diuretics significantly decreases recurrent stroke events, and no significant association between BP reduction and all adverse outcomes was found [14]. It is apparent that the benefit of ACEI plus diuretics for secondary prevention of stroke is explained by mechanisms beyond the effects of lowering BP alone. The underlying mechanisms may be the divergent cardiovascular effects of ACEI [15], and the ability of diuretics to reduce proteinuria and protect the vascular endothelium [16]. Additionally, the presence of a J-shaped relationship between BP and risk of recurrent stroke is, to a certain degree, confirmed by previous research [17]. Under this context, in order to effectively regulate BP for reducing stroke recurrence, it is urgent to find an alternative that will affect multiple targets.

Acupuncture, with a long history of development in Chinese medicine, is becoming the focus of clinical researchers as an alternative for treating hypertension [18, 19]. Acupuncture-induced regulation of BP has been found to involve peripheral and central neural systems [20] and immune modulation mechanisms [21]. Its multiple-target features might explain the potential of acupuncture in effectively regulating BP to reduce stroke recurrence.

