## Methods/design

### Study design and setting

Our study is a prospective, multicenter, subject-, assessor-, and analyst-blinded, pragmatic randomized controlled trial. The research period lasts from May 2015 to May 2020 (201507001-08). Five centers from five cities will be involved in recruitments, treatments, and assessments. Informed consent will be obtained after screening for eligibility, then baseline assessments will be conducted before randomization (details in Table 1). Eligible patients will be allocated, in a 1:1 ratio using a dynamic randomization procedure, into a BP-lowering acupuncture therapy group (experimental group) and a control group. After randomization, the patients in the experimental group will be additionally treated by the *HuoXueSanFeng* needling method (a BP-lowering regimen) plus the “*XingNaoKaiQiao*” needling method [34] (a formula for stroke) over 12 weeks, whereas the control group will be only given the *XingNaoKaiQiao* needling method for 12 weeks. Other routine ischemic stroke treatments in both groups will be provided. During the whole process of our study, the antihypertensive medications will be adjusted based on the BP level in the two groups (details displayed in the “Antihypertensive medication adjustment” section). The primary outcome will be all recurrent stroke cases over a follow-up period of 9 months after receiving 12-week acupuncture treatments. Our protocol presentation is in accordance with the Standard Protocol Items: Recommendations for Interventional Trials 2013 (SPIRIT 2013) guidelines. The study flowchart is presented as Fig. 1.

**Table 1 Tab1:** Study schedule

Period	Screening	Baseline	Treatment (weeks 1–12)		Follow-up (weeks 13–48)	
Week	Week 0	Week 0	Week 6	Week 12	Week 24	Week 48
Eligibility	×					
Demographic medical history	×					
Informed consent		×				
Basic laboratory test®	×			×	×	
24-h ABPM		×	×	×		
TCM syndrome score, SF-36		×	×	×		
NIHSS, BI		×	×	×		
ESRS		×				×
Follow-up BP					×	×
Recurrence of stroke						×
NO, ET, Hcy, sCD40L, Copeptin		×		×	×	
ECG		×		×	×	
Chest X-ray		×				
Color Doppler ultrasound®		×		×		
All-cause mortality rate						×
Combined diseases and drugs	Record at any time					
Antihypertensive medication adjustment	Record at any time					
Adverse event	Record at any time					
Daily BP	Record everyday (based on BP diary)					
Safety of acupuncture	Record at any time					
Patients’ compliance				×		

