### Outcome assessments

The assessors are blinded to grouping. The primary outcome will be all cases of recurrent stroke over a follow-up period of 9 months after receiving 12-week acupuncture treatments. Secondary endpoints, such as 24-h ambulatory BP, TCM syndrome score, Short Form 36-item Health Survey (SF-36) results, National Institute of Health Stroke Scale (NIHSS) and Barthel Index (BI) scale scores will be assessed at baseline, 6 weeks, and 12 weeks post initiating treatments; serum nitric oxide (NO), endothelin (ET), homocysteine (Hcy), soluble CD40 ligand (sCD40L), and copeptin levels and cardiac ultrasound, carotid artery ultrasound, transcranial Doppler, and lower extremity ultrasound results will be evaluated at baseline and 12 weeks after treatment. Other safety indicators including baseline general physical examination, blood, urine, and stool routine tests, coagulation function, D-dimer level, liver and kidney function, electrocardiograph as well as a chest X-ray will also be examined 12 weeks after randomization. At 6 months after randomization, blood, urine, and stool routine tests, coagulation function, D-dimer level, liver and kidney function, electrocardiograph, NO, ET, Hcy, sCD40L, and copeptin tests will be re-checked, with some hope of improving patients’ adherence to treatment. All-cause mortality will also be evaluated during the follow-up period. The Essen Stroke Risk Score (ESRS) will be additionally assessed at baseline and 1 year post randomization.

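### The serious-adverse-event rule unblinds without exempting study outcomes, so as written it would reveal the arm for primary-outcome strokes and deaths while most other patients stay blinded

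*Protocol article*

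**What the plan says.** The rule is in the Patient safety section: "If serious AEs do occur, the grouping will be un-blinded and we will report the AE to the project leader (PL") and to the Ethics Committee, "who will make a decision on whether the participant needs to be withdrawn from the study, or whether the trial should be adjusted or terminated". The paragraph begins with events seen during needling: "In the process of acupuncture treatment, possible adverse events (AEs) including subcutaneous hematoma, infection, alcohol allergy, etc".

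Table 1, in the section on study design and setting, has the entry "Adverse event Record at any time", in a schedule whose follow-up runs to week 48.

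Under Outcome assessments, "The primary outcome will be all cases of recurrent stroke over a follow-up period of 9 months after receiving 12-week acupuncture treatments". All-cause mortality is also evaluated in follow-up, and the statistical methods section divides deaths into stroke and non-stroke causes.

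On blinding, the same outcome section states "The assessors are blinded to grouping". The study design section describes blinding of patients, assessors and analyst. The statistical methods section gives the analysis to a third party who does not know the allocation, and the data management section masks the assistant who enters the data.

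Serious is not defined. The Background says "Recurrent stroke demonstrates higher mortality and disability rates than the previous stroke".

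**The concern.** A code break is normally kept for cases where someone needs to know the arm. Here the occurrence of a serious event is enough. In a trial whose primary outcome is itself a grave clinical event, unblinding then becomes tied to the outcome: patients who have a stroke lose their blind, and most of those who do not have one keep it.

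Two things are at stake. The first is outcome judgement. Recurrences come to light through monthly telephone follow-up, and a suspected recurrence or a cause of death has to be classified by someone. If that person can learn the arm, the classification is open to influence. The second is trial conduct. The project leader would see the arm for endpoint events and also helps decide whether a patient leaves the study and whether the trial changes or ends. The article does not say who else learns the code once it is broken.

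**Working it through.** **1. Does the rule reach the primary outcome?**

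- Condition: any serious adverse event (Patient safety). The sentence limits neither the time nor the type of event.
- Period: adverse events are recorded at any time in a schedule to week 48 (Table 1), which includes the follow-up in which recurrent strokes are counted.
- Seriousness: undefined. On the ordinary meaning (death, hospitalisation, disability), and given the Background's remark on the mortality and disability of a recurrent stroke, stroke and death qualify. This is an inference.
- Exemption: none appears anywhere in the article.

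Read as written, the rule covers recurrent stroke and death.

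**2. The plan's own sample size, as a check on the inputs**

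Inputs from the section on sample size and statistical methods: 16% against 7%, 80% power, two-sided 5%, 197 per group, 15% dropout, 480 recruited. Allocation is 1:1.

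With pooled variance and no continuity correction, and a mean rate of (0.16 + 0.07)/2 = 0.115:

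n = [1.960 × √(2 × 0.115 × 0.885) + 0.8416 × √(0.16 × 0.84 + 0.07 × 0.93)]² / 0.09²
= (0.884 + 0.376)² / 0.0081 ≈ 196.1, rounded up to 197.

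This reproduces the stated figure. For dropout, 394/0.85 = 463.5, or 464, so 480 is enough; 480 × 0.85 = 408, or 204 per arm.

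**3. How many primary events would be unblinded?**

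If every recurrent stroke counts as serious:

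| Patients per arm | Control, 16% | Experimental, 7% | Total |
|---|---|---|---|
| 197 (minimum for analysis) | 31.5 | 13.8 | 45.3 |
| 204 (after 15% dropout) | 32.6 | 14.3 | 46.9 |
| 240 (all randomised) | 38.4 | 16.8 | 55.2 |

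This gives about 45 to 55 events. A patient without a stroke is unblinded only after death or some other serious event.

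**4. How sensitive is the primary comparison to a few classifications?**

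Take the expected 32 against 14 events of 197 and remove control events only:

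| Control events removed | Counts | Chi-square p (uncorrected) | Fisher p |
|---|---|---|---|
| 0 | 32 v 14 | 0.005 | 0.007 |
| 5 | 27 v 14 | 0.032 | 0.047 |
| 6 | 26 v 14 | 0.045 | 0.065 |
| 7 | 25 v 14 | 0.064 | 0.091 |

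Six (Fisher) or seven (chi-square) one-sided changes would take the expected result past 5%. This shows how little it would take. It does not estimate how much bias would occur.

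**The case against.** The best counter-argument concerns scope. The paragraph opens with events during acupuncture, its examples are needling harms, and it asks for causality with acupuncture. The primary outcome is counted after the 12 weeks of treatment. Strokes and deaths have their own route through telephone follow-up, and Table 1 gives recurrence, mortality, adverse events and safety of acupuncture separate rows. The authors may never have meant endpoint strokes to fall under this rule. That keeps the point conditional, but it does not remove it: the serious-event sentence carries no such limit, and if a narrow scope was intended the text should say so.

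Several stronger readings are tempting, and the article does not support them:

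- *Exactly the primary events lose their blind.* Other serious events are unblinded too, and seriousness is undefined.
- *Assessors or the analyst learn the arm.* No sentence gives them, or the data-entry assistant, the code, and all three are described as masked. The project leader and Ethics Committee are not among those said to be blinded. Arm-aware classification is therefore a risk left open, since no limit on disclosure is stated.
- *The 5% error rate is uncontrolled.* The rule describes safety decisions after individual events. It describes no interim comparison of the primary outcome and no stopping for efficacy. A stopping rule may sit in the full protocol or analysis plan, so its absence from an article is not a finding.
- *Withdrawal after a stroke loses the primary event.* The outcome is binary and has already occurred. The Informed consent section keeps the available data of patients who withdraw, and an intention-to-treat analysis is planned.

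On withdrawal a smaller point stands. A patient withdrawn after a non-stroke serious event could have a later stroke or death that is never recorded, and one withdrawn after a stroke could have a later death that is missed.

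**Conclusion.** The point holds as a fault in a stated rule. The plan unblinds on any serious adverse event, exempts no study outcome and does not restrict who learns the arm. Followed literally, it would reveal the allocation for about 45 to 55 primary events at the planned rates while most event-free patients stay blinded. It would also give that knowledge to a project leader who shares decisions on "whether the participant needs to be withdrawn from the study, or whether the trial should be adjusted or terminated". This is hard to reconcile with the blinding that the article claims.

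The conclusion rests on three assumptions: the sentence means what it says, without the limit to needling harms that its opening might suggest; recurrent stroke and death count as serious in the ordinary sense; and the planned rates apply. The count measures exposure to unblinding and not bias. Biased confirmation of strokes or classification of deaths is possible under the text but is not shown by it.

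**What to change.** Amend the Patient safety section so that:

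1. recurrent stroke and death are reported as outcome events, without automatic unblinding;
2. the code is broken for an individual only when the arm is needed for that patient's care or for required safety reporting;
3. the code is withheld from everyone who confirms strokes, classifies deaths or analyses data;
4. any safety review by arm goes to the Ethics Committee, which already receives these reports, or to another party outside the trial team;
5. patients who stop study treatment after a serious event stay in outcome follow-up unless they withdraw consent.

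The cost is a protocol amendment in wording. The sample size and the primary test are unaffected. The small downside is that the project leader sees serious events without the arm.

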### Data management and quality control

The teaching and research office of epidemiology and statistics of the Chinese People’s Armed Police Force Logistics College is fully responsible for the data management of the project. Prior to the project, the center has been involved in the design of the project, which has been discussed twice monthly with the principle experts in the State Administration of Traditional Chinese Medicine of the People’s Republic of China, and project implementation throughout the process has successfully completed quality control and data management scrutiny. A specific research assistant (RA), who is masked to treatment allocation, will enter the clinical data. Data will be obtained by direct questions to patients, from medical records, and a the patient’s relative or proxy. The personal information of the patients will be kept in the specific files with pre-set codes. Entering data into CRFs and other essential skills was covered during the training session prior to study commencement.

All the researchers will accept centralized and unified training before research implementation to help them become familiar with, and master, the diagnosis, treatment measures and basic assessment skills, in order to improve the researchers’ internal observation consistency. A three-level inspector appointed for the national Chinese Medicine Clinical Research Base Unit, First Teaching Hospital of Tianjin University of TCM, and each subcenter will regularly carry out quality monitoring and supervision throughout the study.

### Dissemination

We plan to publish several Chinese and English articles, and hold one or two seminars yearly to disseminate part of our new findings to health care professionals, the public, and other relevant groups. On the other hand, the participants will be instructed on how to better manage their condition after the results yield useful information. After our trial finishes, we will make an effort to share our findings with the experts from other Chinese medical fields, hoping to benefit them by the drafting of stroke and hypertension guidelines incorporated into the features of TCM.

### Biological specimens

The patients’ blood samples for the inpatient routine tests will be collected and analyzed as usual. For testing serum NO and ET concentrations, about 3–5 ml venous blood will be collected; after centrifugation, the remaining serum will be subpacked into frozen tubes, followed by concise labeling, then kept for no more than 6 months in a refrigerator at −80 °C until final analysis by the chemical reagent corporation.

## Discussion

Acupuncture within Chinese medicine has become a visible international brand of China. Both stroke and hypertension are heavy global disease burdens and both have alarmingly high comorbidities [35] which are associated with a poorer prognosis. Antihypertensive medications have been commonly used for preventing stroke recurrence. However, evidence-based medicine data regarding secondary prevention of stroke by antihypertensives is controversial [14, 36]. Therefore, it is of great clinical significance that our study aims to decrease recurrent stroke using acupuncture, in the hope of increasing western knowledge of acupuncture.

As early as in 1983, the WHO recommended non-drug therapy as the preliminary and auxiliary treatment of mild-to-moderate hypertension [26]. With the enhancement of people’s drug safety awareness, the proportion of non-drug therapy in the treatment of hypertension has gradually increased. Acupuncture, with its advantages of convenience, satisfactory effects and few adverse reactions [37], is attracting increasing clinical attention and is also becoming one of the hotly debated topics in the study of alternative medicine worldwide.

The acupuncture method of *XingNaoKaiQiao* for the treatment of stroke was launched in 1972 by the first, and to date, only Chinese academician of engineering in the acupuncture discipline, [name], who devoted himself to introducing acupuncture to the whole world and developed an international academic team that cooperates with Germany, France, Japan, and Singapore, among other countries. For its internationally substantial contributions, *XingNaoKaiQiao* needling therapy for stroke has been recognized as another special acupuncture technique in addition to acupuncture anesthesia by foreign health care researchers. Besides the confirmed effects for stroke by our own team, the others also reported its encouraging results for stroke patients [38]. With the great success of *XingNaoKaiQiao*, academician [name] gained deeper insight into secondary stroke prevention, and established another acupuncture treatment for hypertension called *HuoXueSanFeng*, the BP-lowering acupuncture regimen used in our trial. Our previous researches have shown that this acupuncture method reduces BP for primary hypertension patients, and its immediate and long-term antihypertensive efficacy is significant for either BP-lowering or improving the patients’ clinical symptoms [27–33]. So, here we also want to investigate the BP-controlling effect of *HuoXueSanFeng*, especially regarding its sole efficacy, in a larger sample size population. In this study, both *XingNaoKaiQiao* and *HuoXueSanFeng* needling therapy are performed over the 12-week treatment period; *XingNaoKaiQiao* therapy is a general treatment for stroke with a high credibility, its free treatment here will enhance adherence with participation. Additionally, because both groups are needled, subject blinding should be ensured, minimizing the placebo effect of acupuncture.

Of note, in our trial, we cautiously selected three secondary endpoints, namely, Hcy, sCD40L, and copeptin levels, which were closely related to stroke recurrence. Elevated Hcy levels have been reported to be indicative of an increased risk for ischemic strokes and recurrent strokes [39]. sCD40L appears to be an independent predictor for stroke recurrence [40]. Copeptin has been studied to be a predictor of both severity at admission and 1-year stroke recurrence in stroke patients [41]. Assessing the influence of our study treatment on them might be reflective of the effects on stroke recurrence via acupuncture lowering hypertension.

The multicenter approach of our study allows more generalisable interpretation of the results and the usage of standardized, cross-culturally adapted assessment allows comparison and pooling of all study data from different trial centers. Considering methodological and ethical reasons, acupuncture will be delivered to both groups to prevent bias through potential placebo effects. To improve operation and observation consistency, the research sets strict rules that must be followed.

The unavoidable weaknesses of our trial are as follows: (1) the five hospitals are located in different cities, so the standard of acupuncture manipulation will differ between them. Therefore, strict training and supervision will be implemented to ensure unified and consistent operation as far as possible, (2) despite the subject- and assessor-blinding, there are still some patients who will likely know which group they are in; therefore, we would keep the patients separate when receiving treatment to avoid them talking to each other; (3) after completion of the 12-week treatment, a 9-month follow-up will be conducted. This time span means that participant compliance could be a problem. Accordingly, we have designed the BP diary and regular telephone follow-up to try to minimize this.

## Abbreviations

ABPM: Ambulatory blood pressure monitoring
ACEI: Angiotensin-converting enzyme inhibition
AEs: Adverse events
ANOVA: Analysis of variance
BI: Barthel Index
BP: Blood pressure
CRFs: Case Report Forms
ECG: Electrocardiograph
ESRS: Essen Stroke Risk Score
ET: Endothelin
Hcy: Homocysteine
IEC: Independent Ethics Committee
ITT: Intention-to-treat
NIHSS: National Institute of Health Stroke Scale
NO: Nitric oxide
PL: Project leader
PP: Per-protocol
RA: Research assistant
RCT: Randomized controlled trial
sCD40L: Soluble CD40 ligand
SF-36: Short Form 36-item Health Survey
SPIRIT 2013: Standard Protocol Items: Recommendations for Interventional Trials 2013
TCM: Traditional Chinese medicine.
